### Interventions

#### Study arm 1: best NHS care diet

All dietetic advice will be face-to-face or via video calls or the telephone. Participants will receive one-to-one personalised written and verbal advice from a dietitian to follow NICE diet and physical activity recommendations.^6 7^ Dietitians and midwives will receive training to ensure standardised delivery of information in clinic, and standardised patient information leaflets will be supplied to include information about increased fruit/vegetable intake, low-GI foods and a reduction in free sugars. Information will include advice about the importance of regular meals; dietary advice aims to ensure that participants include at least 70 g protein/28 g fibre, and predominantly monounsaturated and polyunsaturated fats as per American Diabetes Association recommendations.^32^ Participants will be advised to be physically active, for example, walking for 30 min after a meal. Participants will receive ongoing dietetic education and support every 2 weeks until delivery. This level of support is higher than typically provided in NHS GDM antenatal clinics due to limited resources but has been used to reflect best NHS care. They will receive suggested menus and recipes to follow the NICE recommended healthy diet for GDM. Participants will be asked to measure their capillary glucose four times each day and their ketones on two random (recorded) days of the week of their choosing (online supplemental file 3).

10.1136/bmjopen-2023-078264.supp3Supplementary data

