**Method and analysis:**

We aim to recruit 48 women with GDM diagnosed between 24 and 30 weeks gestation from antenatal clinics at Wythenshawe and St Mary’s hospitals, Manchester Foundation Trust, over 13 months starting in November 2022. Participants will be randomised (1:1) to ILED (2 low-energy diet days/week of 1000 kcal and 5 days/week of the best NHS care healthy diet and physical activity advice) or best NHS care 7 days/week until delivery of their baby. Primary outcomes include uptake and retention of participants to the trial and adherence to both dietary interventions. Safety outcomes will include birth weight, gestational age at delivery, neonatal hypoglycaemic episodes requiring intervention, neonatal hyperbilirubinaemia, admission to special care baby unit or neonatal intensive care unit, stillbirths, the percentage of women with hypoglycaemic episodes requiring third-party assistance, and significant maternal ketonaemia (defined as ≥1.0 mmol/L). Secondary outcomes will assess the fidelity of delivery of the interventions, and qualitative analysis of participant and healthcare professionals’ experiences of the diet. Exploratory outcomes include the number of women requiring metformin and/or insulin.

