#### Study arm 2: ILED

Participants will receive the same level of dietetic support as the best NHS care group. They will be given advice on adopting an ILED which involves 2 non-consecutive low-energy diet days/week (1000 kcal to include 100 g low-GI carbohydrate and 70 g of protein) and 5 days/week of the NICE healthy eating low-GI diet and physical activity recommended for the best NHS care group. The low-energy days involve women selecting a set number of portions of protein, carbohydrate, fat, fruit, vegetables and dairy/dairy alternatives as described in previous studies.^33^ Each low-energy day includes ~210 g of lean protein foods, 3–4 portions of wholegrain carbohydrates, 1×7 g portion of fat, 5 portions of vegetables, 2 of fruit and 3 of dairy/dairy alternatives. Food and drink will be self-selected and not provided by the study team. Participants will be provided with comprehensive food lists, advice on portion sizes for the low-energy days and suggested menus and recipes to follow for both the low-energy and NICE recommended healthy diet days (online supplemental file 4). Both diets can be successfully adapted for people of different ethnicities and those following omnivorous, vegetarian and vegan diets. Participants will be asked to measure their capillary glucose four times each day and their ketones on (and the morning after) the two low-energy days (online supplemental file 3).

10.1136/bmjopen-2023-078264.supp4Supplementary data

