### Outcomes

#### Primary outcomes

Uptake rate measured as a percentage of eligible participants who consent to take part, including the proportion of women who were screened who did not meet the eligibility criteria, and the number of women who did not give consent to take part.Recruitment rate measured as the number of eligible participants who consent to take part per month.Retention rate measured as the number of randomised participants who complete the trial (those who attend the final visit) and the percentage of participants who attend all eight visits.Adherence to the dietary interventions assessed from self-reported adherence to the potential low-calorie days between randomisation and delivery.Completion of self-assessed glucose and ketone readings assessed as a percentage of the required readings.Safety outcomes:Percentage of women following ILED/best NHS care with hypoglycaemia (episodes of blood glucose of <3.0 mmol/mol) and hypoglycaemia requiring third-party assistance as measured by participants.Percentage of women who develop significant ketonaemia in both groups (defined as ≥1.0 mmol/L) as measured by participants.Percentage of neonatal hypoglycaemic episodes requiring intervention (blood glucose checked 2 hours post delivery and 2 hours thereafter for 12 hours according to local protocol), neonatal birth weight, gestational age at delivery, hyperbilirubinaemia/jaundice and/or admission to Special Care Baby Unit or neonatal intensive care, and stillbirths.The incidence and rate of other adverse events (eg, headaches, lethargy, constipation or complications requiring hospital admission) between the start of the trial intervention and delivery recorded as mild, moderate and severe, as defined by Common Terminology Criteria for Adverse Events (CTCAE V.5).^34^ Hospital admission for routine labour and delivery will not be classified as an adverse event.

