#### Statistical methods

A statistical analysis plan specifying the full details of the primary and secondary outcomes, other variables and methods will be produced prior to trial analysis. The main analysis will be conducted via intention-to-treat population and will not undertake any significance tests. Descriptive, graphical (summary) and basic statistics (eg, (1) number, frequencies and percentages, (2) mean and SD, or (3) median and quartiles as appropriate) will be presented as appropriate for each group, respectively, for group difference jointly, and for each stratum. Per-protocol analysis will be considered as a secondary analysis. Levels of missing data will be investigated and used to inform future studies. No imputation will be used. The end of study questionnaire will be analysed using appropriate descriptive statistics for closed questions and key themes will be extracted without formal analysis from open questions to inform future research.

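### Ketonaemia is compared between arms as an ever/never percentage although the ILED arm is scheduled to test ketones on about twice as many occasions, which pushes its figure upward

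*Protocol article*

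**What the plan says.** In the protocol article, Study arm 1 asks best NHS care participants to measure "their ketones on two random (recorded) days of the week of their choosing". Study arm 2 asks ILED participants to measure "their ketones on (and the morning after) the two low-energy days". Because the ILED arm follows "2 non-consecutive low-energy diet days/week", each following morning falls on a different day from either low-energy day, so the ILED schedule covers four days a week and the control schedule two.

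The safety outcomes listed under Primary outcomes include: "Percentage of women who develop significant ketonaemia in both groups (defined as ≥1.0 mmol/L) as measured by participants". This counts women, not readings: one qualifying reading at any time makes a woman a case.

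Statistical methods plans descriptive summaries for each group, "for group difference jointly, and for each stratum", and "will not undertake any significance tests". Nothing in the article limits the ketonaemia outcome to matched readings or relates it to the number of readings taken.

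**The concern.** An ever/never percentage can only rise as readings are added. If two arms have the same risk per reading, the arm that tests more often is expected to show more women with ketonaemia. The described group difference would then mix any effect of the diet with an effect of the testing schedule.

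Two features add to this. A next-morning reading tied to the test day is specified in one arm only. The control test days are described as random and also as the participant's own choice, and a day a woman picks is not random. If she picks days for convenience or because of how she has eaten, the control readings may not represent her usual week.

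Safety is the first-named aim of the trial, and the results are meant to inform a definitive trial. A ketonaemia difference that partly reflects test frequency could be carried forward as a property of the diet.

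**Working it through.** The protocol states no expected figure for ketonaemia, so there is none to reproduce. The check asks what gap the schedule alone would create if the diet had no effect on ketones.

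**Inputs from the protocol article**
- Control occasions: 2 per week (Study arm 1).
- ILED occasions: 2 low-energy days + 2 following mornings = 4 per week (Study arm 2).
- Women: 24 per arm (Sample size).
- Start of monitoring: the abstract gives "48 women with GDM diagnosed between 24 and 30 weeks gestation". End: delivery.

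**Assumptions, not in the protocol**
- One reading per occasion, all readings completed.
- Delivery at 37 to 40 weeks, so monitoring lasts from 37 − 30 = 7 to 40 − 24 = 16 weeks; 10 and 12 weeks are used as middle values.
- The risk q that a reading is 1.0 mmol/L or more is equal in both arms; 0.5%, 1% and 2% are shown.
- Within-woman correlation of readings ρ: 0, 0.02, 0.1 and 0.3.

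**Independent readings.** With n readings, P(ever) = 1 − (1 − q)^n.

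At 10 weeks, n = 20 (control) and 40 (ILED). For q = 1%: 1 − 0.99^20 = 18.2% and 1 − 0.99^40 = 33.1%, a gap of 14.9 points, or about 4.4 against 7.9 women of 24.

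At 12 weeks, n = 24 and 48:

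| q | Control | ILED | Gap (points) |
|---|---|---|---|
| 0.5% | 11.3% | 21.4% | 10.0 |
| 1% | 21.4% | 38.3% | 16.8 |
| 2% | 38.4% | 62.1% | 23.7 |

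Across 7 to 16 weeks at q = 1%, the gap runs from 11.4 to 19.9 points.

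**Correlated readings.** Let each woman's risk follow a beta distribution with a = q(1 − ρ)/ρ and b = (1 − q)(1 − ρ)/ρ. Then P(ever) = 1 − B(a, b + n)/B(a, b), where B is the beta function. For example, q = 1% and ρ = 0.1 give a = 0.01 × 9 = 0.09 and b = 0.99 × 9 = 8.91.

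At q = 1%:

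| ρ | Control vs ILED, 10 weeks | Gap, 10 weeks | Gap, 12 weeks |
|---|---|---|---|
| 0 | 18.2% vs 33.1% | 14.9 | 16.8 |
| 0.02 | 15.6% vs 25.6% | 10.0 | 10.8 |
| 0.1 | 10.3% vs 14.5% | 4.2 | 4.3 |
| 0.3 | 5.6% vs 7.0% | 1.4 | 1.4 |

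At ρ = 0.1 and 10 weeks the gap is 24 × 0.042, or about one woman per arm of 24.

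**Equal schedules.** With the same number of readings per week in both arms and equal q, the expected gap is 0 at every ρ.

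**The case against.** The case on the other side is substantial, and parts of it stand.

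- **Readings per day are not given.** Both arms refer to online supplemental file 3, which is not shown. If it sets a different number of readings per test day in the two arms, the 2:1 ratio changes. Control readings may also be taken in the morning. Both points stand.
- **Actual counts may differ from the schedule.** If ILED women test only around low-energy days they complete, missed days reduce their readings. At 50% completion, 4 × 0.5 = 2 occasions a week, which equals the control schedule. This stands, and it makes the ketonaemia percentage depend on adherence, a further reason to report reading counts.
- **Readings from one woman are probably correlated.** A reader might infer from the independent model that the schedule doubles the ILED percentage or adds 10 to 24 points. That is the upper end of the range; moderate correlation removes most of the gap.
- **The arms can be compared in other ways.** A reader might infer that a true effect cannot be separated from extra testing. That is too strong: fasting beta-hydroxybutyrate is among the study bloods (Blood samples), and fasting bloods are compared at baseline, 36–37 weeks and 12 weeks post delivery (Exploratory outcomes). Only one of those follow-up points falls in late pregnancy, so this supports the self-measured outcome but does not replace it.
- **No decision rule uses it.** There are no significance tests, the trial is not powered for differences, and Table 1 has no ketonaemia criterion. The bias from count also runs against ILED, so it would not falsely reassure. This limits the severity, but a described group difference carries the same bias as a tested one.
- **The analysis plan may deal with it.** It may, but the outcome and both schedules are fixed in this article, and no later plan can recover control readings that were never scheduled. The completion outcome does not help: it is a percentage of required readings, and if the requirement differs by arm, full completion in both still leaves unequal counts.

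Closer testing around low-energy days is reasonable surveillance. The fault lies in the between-arm comparison. Nor does a shorter time on study bias the contrast, as a reader might suppose: randomisation balances it in expectation.

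**Conclusion.** The point holds as a bias of known direction and uncertain size. Under the schedule as written, with one reading per occasion, ILED women have about four chances a week to cross 1.0 mmol/L and control women two, so equal risk per reading still gives a higher ever/never percentage in ILED. At an assumed 1% per reading over 10 to 12 weeks, the spurious gap ranges from about 15–17 points with independent readings to about 1.4 points at a within-woman correlation of 0.3. The protocol gives neither the risk nor the correlation, so no single figure should be quoted.

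The comparison should be corrected because it is a named safety outcome and the correction is cheap. It does not invalidate the trial, and no progression decision depends on it.

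**What to change.** Leave ILED ketone monitoring as written and change the comparison.

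1. Base the between-arm ever/never contrast on a pre-specified like-for-like set: test-day readings only, with the same number per week in both arms.
2. Report the ILED morning-after readings separately.
3. Give the number of readings in each arm and the rate of readings of 1.0 mmol/L or more per reading taken. State that this rate corrects for count but not for timing, since ILED readings still cluster around low-energy days.
4. Present fasting beta-hydroxybutyrate by arm as a supporting symmetric comparison.
5. Reconcile the description of the control test days, which are called both random and self-chosen.

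Items 1 to 4 use data already planned. The cost is a little more analysis and fewer ILED readings in the between-arm contrast; item 5 is a wording change.

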#### Study arm 2: ILED

Participants will receive the same level of dietetic support as the best NHS care group. They will be given advice on adopting an ILED which involves 2 non-consecutive low-energy diet days/week (1000 kcal to include 100 g low-GI carbohydrate and 70 g of protein) and 5 days/week of the NICE healthy eating low-GI diet and physical activity recommended for the best NHS care group. The low-energy days involve women selecting a set number of portions of protein, carbohydrate, fat, fruit, vegetables and dairy/dairy alternatives as described in previous studies.^33^ Each low-energy day includes ~210 g of lean protein foods, 3–4 portions of wholegrain carbohydrates, 1×7 g portion of fat, 5 portions of vegetables, 2 of fruit and 3 of dairy/dairy alternatives. Food and drink will be self-selected and not provided by the study team. Participants will be provided with comprehensive food lists, advice on portion sizes for the low-energy days and suggested menus and recipes to follow for both the low-energy and NICE recommended healthy diet days (online supplemental file 4). Both diets can be successfully adapted for people of different ethnicities and those following omnivorous, vegetarian and vegan diets. Participants will be asked to measure their capillary glucose four times each day and their ketones on (and the morning after) the two low-energy days (online supplemental file 3).

10.1136/bmjopen-2023-078264.supp4Supplementary data

### Outcomes

#### Primary outcomes

Uptake rate measured as a percentage of eligible participants who consent to take part, including the proportion of women who were screened who did not meet the eligibility criteria, and the number of women who did not give consent to take part.Recruitment rate measured as the number of eligible participants who consent to take part per month.Retention rate measured as the number of randomised participants who complete the trial (those who attend the final visit) and the percentage of participants who attend all eight visits.Adherence to the dietary interventions assessed from self-reported adherence to the potential low-calorie days between randomisation and delivery.Completion of self-assessed glucose and ketone readings assessed as a percentage of the required readings.Safety outcomes:Percentage of women following ILED/best NHS care with hypoglycaemia (episodes of blood glucose of <3.0 mmol/mol) and hypoglycaemia requiring third-party assistance as measured by participants.Percentage of women who develop significant ketonaemia in both groups (defined as ≥1.0 mmol/L) as measured by participants.Percentage of neonatal hypoglycaemic episodes requiring intervention (blood glucose checked 2 hours post delivery and 2 hours thereafter for 12 hours according to local protocol), neonatal birth weight, gestational age at delivery, hyperbilirubinaemia/jaundice and/or admission to Special Care Baby Unit or neonatal intensive care, and stillbirths.The incidence and rate of other adverse events (eg, headaches, lethargy, constipation or complications requiring hospital admission) between the start of the trial intervention and delivery recorded as mild, moderate and severe, as defined by Common Terminology Criteria for Adverse Events (CTCAE V.5).^34^ Hospital admission for routine labour and delivery will not be classified as an adverse event.

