## Introduction

### Background

In the UK up to 16% of pregnant women develop gestational diabetes mellitus (GDM) and the incidence is rising, in part due to increasing rates of obesity and maternal age.^1 2^ GDM is associated with maternal and neonatal complications (the risk increases with poor glycaemic control), including macrosomia, shoulder dystocia, caesarean sections, neonatal hypoglycaemia and/or hyperbilirubinaemia, preterm delivery, pre-eclampsia and stillbirth.^2^ Women who have had GDM have an estimated 7-fold to 10-fold risk of developing type 2 diabetes (T2DM) later in life, and their children have a higher risk of developing adult obesity and T2DM.^2–4^

Excessive weight gain in pregnancy is a particular problem for women with GDM.^5^ Harper *et al* demonstrated that, in women with GDM, every additional 1 lb/week gained following diagnosis of GDM resulted in a 36%–83% increased risk of pre-eclampsia, caesarean section, macrosomia and large for gestational age babies.^5^ Such studies highlight the importance of adequate weight control throughout pregnancy in women with GDM in order to reduce both maternal and neonatal complications.

First-line therapy for GDM is diet and physical activity. National Institute for Health and Care Excellence (NICE) guidance encourages a healthy diet with increased fruit and vegetables, low-glycaemic index (GI) foods, reduced refined sugars, regular mealtimes and regular physical activity.^6 7^ These dietary measures fail to achieve glycaemic targets in ~30% of women who require medication with metformin and/or insulin.^8^ A range of dietary approaches have been studied including daily diets promoting low-GI diets (limiting refined and promoting complex carbohydrates), continuous modest energy restriction (1800 kcal/day) and low carbohydrate diets.^9^ There is currently no strong evidence base for any particular dietary regimen to improve outcomes in GDM.

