#### Adverse events

Participants in both groups will be asked about any adverse effects that they have experienced at each visit. These will include, but are not limited to, the potential effects of a low-energy diet, for example, headache, lethargy, dizziness, constipation, indigestion, poor concentration and hunger. Adverse events will be graded as per CTCAE V.5.^34^ Participants will be issued with a participation/emergency card with emergency contact details for the research team to be carried at all times and to be shown to the attending physician in case of emergency admission to hospital. All participants will be issued with clear instructions as to how to manage a hypoglycaemic and/or ketonaemic event (online supplemental file 5).

10.1136/bmjopen-2023-078264.supp5Supplementary data

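### The adverse-event outcome closes at delivery and stillbirth is the only death listed, so no safety outcome reports a neonatal death as a death or counts a postpartum maternal admission

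*Protocol article*

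**What the plan says.** The safety outcomes stand under Primary outcomes in the protocol article. Two of their items matter here.

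- **Other adverse events.** The examples given are "headaches, lethargy, constipation or complications requiring hospital admission". Events count when they occur "between the start of the trial intervention and delivery recorded as mild, moderate and severe". The end date is explicit.
- **Neonatal items.** These are neonatal hypoglycaemia, birth weight, gestational age, jaundice, "and/or admission to Special Care Baby Unit or neonatal intensive care, and stillbirths". Only hypoglycaemia has a stated period ("blood glucose checked 2 hours post delivery and 2 hours thereafter for 12 hours according to local protocol"). Jaundice and unit admission have no end date, and the delivery cut-off is not attached to them.

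The abstract's list ends its neonatal part in the same way: "admission to special care baby unit or neonatal intensive care unit, stillbirths". Stillbirth is the only death named in either place.

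The Adverse events section sets a different scope for collection: "Participants in both groups will be asked about any adverse effects that they have experienced at each visit". It states no stop at delivery. Study contact goes on after birth: the Exploratory outcomes include blood tests at 12 weeks post delivery, and the Qualitative substudy section refers to a postpartum visit for all participants.

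**The concern.** Collection and reporting do not cover the same period. A woman can be asked at her postpartum visit about something that happened after the birth, and the outcome definition then leaves it out. For symptoms of a low-energy day that does no harm, because the diet stops at delivery. For serious events it matters more. Perinatal deaths are split at birth, with those before it counted by name and those after it not named. A mother's hospital admission counts the day before delivery but not the week after.

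Safety comes first in the stated aim, and the results are meant to inform a larger trial. Table 1 has no safety criterion for progression, so the safety conclusion will be a descriptive statement drawn from this list. It can be no more complete than the list is.

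**Working it through.** The plan gives no figure on this point, so the check is to follow individual events through the outcome definitions as written.

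| Event | Other adverse events (ends at delivery) | Neonatal items (no delivery cut-off) | Result |
|---|---|---|---|
| Maternal admission for a complication before delivery | Counted | – | Counted |
| Maternal admission after delivery | Outside the window | – | In no reported safety outcome |
| Stillbirth | – | Counted by name | Counted as a death |
| Live-born baby admitted to a neonatal unit, then dies | Outside the window | Counted as a unit admission | Counted, but not as a death |
| Live-born baby dies without unit admission | Outside the window | Not named | Not counted as a death |
| Baby later treated for jaundice or admitted to a neonatal unit | Outside the window | Counted, end date unstated | Counted, period unclear |

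The second, fourth and fifth rows are the gap. The last row shows where the list does reach past birth, and that it does not say how far.

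The two rules on timing, side by side:

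1. Primary outcomes: from the start of the intervention to delivery.
2. Adverse events: at each visit, with no end stated, in a study that has a postpartum visit.

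Both can be followed in the data collection. The first then discards from the outcome whatever the second picks up after birth.

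On size, the document gives no rate for neonatal death or for postpartum admission, so an expected number of missed events cannot be derived. Assuming one baby per woman, and using the planned sample (48 women, 24 per arm):

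- One death is 1/24 = 4.2% of an arm and 1/48 = 2.1% of the trial. The expected count over the whole trial is below one for any assumed rate under 2.1%.
- With complete capture and no deaths in an arm of 24, the one-sided 95% upper limit is 1 − 0.05^(1/24) = 11.7%.

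The trial therefore cannot estimate such a rate in either case. What is at issue is whether a rare serious event, if it happens, is visible in the report.

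**The case against.** The strongest defence is that the design is coherent. The diet ends at delivery, the adverse-event window covers the time on diet, and separate neonatal items take over from birth. That stands for diet-related symptoms. It does not explain why the neonatal items name one kind of death only, or why a complication admitting the mother after birth has no place.

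A second defence is that this is a journal article. Handling of serious events may be set out in the full protocol; the schedule of assessments and the participant instructions for hypoglycaemia and ketonaemia are not visible either. This also stands, and it limits the point. An explicit cut-off in a primary outcome is nevertheless a stated rule, not a detail left to another document.

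Three stronger readings are tempting and should not be drawn:

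- A reader might infer that a baby's readmission falls in no safety outcome. The documents do not support that, since jaundice and neonatal unit admission have no delivery cut-off.
- A reader might measure the gap as the share of follow-up that lies after delivery. That share depends on assumed entry and delivery dates, and it measures calendar time, not missed events.
- The Background lists complications of gestational diabetes ("including macrosomia, shoulder dystocia, caesarean sections, neonatal hypoglycaemia and/or hyperbilirubinaemia, preterm delivery, pre-eclampsia and stillbirth"), and shoulder dystocia is in no outcome list. Nothing requires every background risk to be an outcome in a feasibility trial, and birth weight and mode of delivery are already collected.

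**Conclusion.** The point holds as a gap in the outcome definitions. Read literally, the list reports a neonatal death at most as a unit admission and omits a postpartum maternal admission, while the Adverse events section sets no matching limit on what is asked. Neonatal admission also lacks an end date.

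A reader might go further and conclude that these events would go unrecorded or unreported to the sponsor. The article does not show that: women are asked at each visit, and serious-event reporting may be specified elsewhere.

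The likely number of events is unknown and, in 48 women, may well be none. The case for change rests on the trial's own safety aim and on the low cost of the remedy. It assumes that the postpartum visit at about 12 weeks takes place as described and is among the visits at which adverse effects are asked about.

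**What to change.** Four changes to the outcome wording:

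1. Keep the start-to-delivery window for diet-related symptoms.
2. For serious events in mother and baby (death, hospital admission, life-threatening events), run the window to the existing postpartum visit, so that the Primary outcomes and Adverse events sections agree.
3. Replace stillbirths with stillbirths and neonatal deaths, in the outcome list and in the abstract.
4. State the date up to which neonatal unit admission is counted.

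If the full protocol already defines serious-event reporting to a later date, the outcome can adopt that date. The cost is a few more fields on the case report form at a visit that is already planned. Some postpartum events unrelated to the diet will enter the table; reporting events before and after delivery in separate rows keeps them apart. Neither treatment, visit schedule nor sample size changes.
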